## Abstract

**Background:**

Immunotherapy targeting the PD-1/PD-L1 pathway is a standard of care in a number of metastatic malignancies, but less than a fifth of patients are expected to respond to ICIs (Immune Checkpoint Inhibitors). In a clinical trial, combining the anti-TIGIT (*T cell immunoreceptor with Ig and ITIM domains*) Mab (monoclonal antibody) tiragolumab with atezolizumab improved outcomes in non-small cell lung cancer. In preclinical models, SBRT (Stereotactic Body Radiation Therapy) could increase expression levels of the inhibitory co-receptors TIGIT and PD-L1. We aim to assess the combination of tiragolumab with atezolizumab and SBRT in metastatic, previously treated by ICIs, non-small cell lung cancer, head and neck cancer, bladder cancer, and renal cell cancer.

**Methods:**

This phase I study (ClinicalTrials.gov NCT05259319) will assess the efficacy and safety of the combination of atezolizumab with tiragolumab and stereotactic body radiation therapy in patients with histologically proven metastatic non-small cell lung cancer, renal cell cancer, bladder cancer, and head and neck cancer previously treated. First part: 2 different schedules of SBRT in association with a fixed dose of atezolizumab and tiragolumab will be investigated only with metastatic non-small cell lung cancer patients (cohort 1). The expansion cohorts phase will be a multicentric, open-label study at the recommended scheme of administration and enroll additional patients with metastatic bladder cancer, renal cell cancer, and head and neck cancer (cohort 2, 3 and 4). Patients will be treated until disease progression, unacceptable toxicity, intercurrent conditions that preclude continuation of treatment, or patient refusal in the absence of progression or intolerance. The primary endpoint of the first phase is the safety of the combination in a sequential or concomitant scheme and to determine the expansion cohorts phase recommended scheme of administration. The primary endpoint of phase II is to evaluate the efficacy of tiragolumab + atezolizumab + SBRT in terms of 6-month PFS (Progression-Free Survival). Ancillary analyses will be performed with peripheral and intratumoral immune biomarker assessments.

**Trial registration:**

This study is registered on ClinicalTrials.gov: NCT05259319, since February 28th, 2022.

**Supplementary Information:**

The online version contains supplementary material available at 10.1186/s12885-023-11534-6.

## Background

ICIs are a key compound in the therapeutic arsenal approved in the metastatic setting for a number of solid malignancies [1–5]. Mabs targeting the immunological synapse currently constitute the first-line standard of care treatment for metastatic non-small lung and head and neck cancer in monotherapy or in combination with chemotherapy [6–8]. Likewise, in the first line setting for metastatic renal clear cell carcinoma, several strategies are available with ICIs combination or ICIs and anti-angiogenic targeted therapies [3]. In the context of metastatic urothelial cancer, ICIs showed a clinical benefit either in maintenance after first-line chemotherapy with no disease progression or in the second-line setting [9, 10]. Although immunotherapy alone or in combination with chemotherapy has revolutionized the treatment of several malignancies, allowing a dramatic OS (Overall Survival) enhancement with a good safety profile, a large proportion of patients are still resistant to such therapies [11].

This lack of efficacy of ICIs has been intensively explored, looking for answers within the tumor microenvironment (TME) and the characterization of tumor-infiltrating lymphocytes (TILs), which brought out the ‘cold’ and ‘hot’ tumor concepts. Considering theses evidences, which testify the central role of the immune context, signatures have been designed and have demonstrated their prognostic values reaching a superior accuracy than the classical AJCC/UICC TNM [12]. Beyond the classical immune checkpoints PD-1, PD-L1, and CTLA4, additional immunomodulatory pathways have been characterized and are currently targeted in order to enhance immunotherapy efficacy. One of these co-inhibitory receptors is the receptor TIGIT which down-regulates T cell and NK function by interacting with its ligands CD155 and CD122 [13]. Tiragolumab is a Mab that binds TIGIT at the immune cell surface, thus preventing inhibitory signal transduction. In the first-line setting of metastatic non-small cell lung cancer, combining tiragolumab with atezolizumab demonstrated a better overall response rate (ORR) and longer PFS than anti-PD-L1 monotherapy, along with a tolerable safety profile [14, 15].

Radiotherapy (RT) has been shown to trigger immunogenic cell death with HMGB1 (High Mobility Group Box 1) release by tumor cells and dendritic cells (DCs) activation through TLR4, allowing a tumor antigen-specific T cell immunity [16]. This is one of the mechanisms that may support the abscopal effect induced by radiation therapy. The abscopal effect is based on the ability of radiation to generate neoantigens (TNAs) expression by tumor cells, allowing their capture by antigen- presenting cells (APCs) such as DCs, which could subsequently prime T cells in secondary lymphoid organs. After activation, migration, and infiltration in both irradiated and non-irradiated tumor metastases, T cells may exert an anti-tumor immune response. Accordingly, combining immunotherapy with radiotherapy is an interesting approach to enhance the abscopal effect [17]. Aware that metastatic lesions are heterogeneous within their different location sites, it is thought that multisite irradiation should be more potent than single-site irradiation in order to unveil more tumor-associated antigens (TAAs) and/or TNAs, thus enhancing the synergic effect between radiotherapy and ICI [18]. Reassuringly, such a combination of SBRT (Stereotactic Body Radiation Therapy) with immunotherapy in the metastatic setting appears to be safe with acceptable toxicity [19]. Although this association shows great promise, it requires optimization of factors such as administration schedule, fractionation, and immunotherapy types.

In preclinical models of CT26 and B16 murine cancers, we assessed the effect of several radiotherapy doses per fraction on PD-L1 and TIGIT expression levels. Results suggest that irradiation using a moderate hypofractionation schedule is more likely to trigger PD-L1 and TIGIT expression, justifying our therapeutic approach that targets both receptors. Furthermore, the triple association of anti-TIGIT, anti-PD-L1, and concomitant RT with a 3 fractions of 8 Gy schedule was correlated with better survival in this model compared to all other 3x8 Gy regimens, i.e., anti-PD-L1 plus RT 3x8 Gy, anti-TIGIT plus RT 3x8 Gy, and RT 3x8 Gy alone [20].

Thus, based on the clinical trial association of tiragolumab and atezolizumab and our preclinical data with additional SBRT, we believe that a trial combining these therapies will be important to confirm the safety and efficacy of such an approach. The rationale supporting this study is provided in Fig. 1.

**Fig. 1 Fig1:**
[figure not shown]
Rationale: SBRT induces immunogenic cell death, which promotes TAAs and/or TNAs uptake by DCs. Then DCs migrate into the DLN in order to prime naive T cells. After activation in the DLN, CD8 T cells join irradiated and non-irradiated lesions to perform their anti-tumor immune function. CD8 T cell: CD8 T lymphocyte; DC: dendritic cell; DLN: draining lymph node; PD-L1: programmed death-ligand 1; PVR: poliovirus receptor; SBRT: stereotactic body radiation therapy; TAA: tumor-associated antigen; TNA: tumor neoantigen; TIGIT: T cell immunoreceptor with Ig and ITIM domains

## Methods

### Study design

This trial will include two parts:

The first part will be a monocentric, open-label, phase I, with the aim of establishing the recommended safety scheme of administration (concomitant or sequential) of tiragolumab + atezolizumab + SBRT. Only patients suffering from metastatic non-small cell lung cancer (cohort 1) will be enrolled in phase I. Other cancers will be studied in the second part of the study.

The second part will be a multicentric study, open-label, expansion cohorts phase under the recommended scheme of administration. Patients from 4 different cohorts (metastatic non-small cell lung cancer, metastatic bladder cancer, metastatic renal cell carcinoma, and metastatic head and neck carcinoma) will be enrolled in the second part.

Patients will be treated until disease progression, unacceptable toxicity, intercurrent conditions that preclude continuation of treatment, or patient refusal in the absence of progression or intolerance. The maximum duration of the treatment with immunotherapy will be 24 months.

### Phase I design

Two different schemes of administration will be investigated:

Sequential administration (scheme 1): SBRT (3 fractions of 8 Gy in 5 days) starting on week 1, followed by the first injection of atezolizumab + tiragolumab at week 2, then every 21 days.Concomitant administration (schema 2): SBRT (3 fractions of 8 Gy in 5 days) starting on week 1, with the first injection of atezolizumab + tiragolumab concomitant to the first radiotherapy fraction, then every 21 days.

Immunotherapies will be administered intravenously: atezolizumab (1200 mg) first, then tiragolumab (600 mg) second. The fixed dose of 600 mg was selected on the basis of available clinical pharmacokinetics, efficacy, and safety data from the combined phase Ia/phase I study (GO30103), with single-agent tiragolumab or tiragolumab in combination with atezolizumab. This dose regimen was used in the CITYSCAPE trial that assessed the atezolizumab and tiragolumab combination in metastatic NSCLC [14, 15]. The study design is provided in Fig. 2.

**Fig. 2 Fig2:**
[figure not shown]
Study design. Sequential schedule (top panel), concomitant schedule (bottom panel)

### Extension cohorts phase design

Sequential or concomitant administration based on the phase I results.

### Progression of the study

The study will start with a 28-day baseline phase.

The end of the study is defined as the date of the last follow-up visit performed by the last patient in the study.

The planned follow-up treatment phase will be 24 months after the last dose of study treatment.

The total duration of the study will be approximately 96 months, including about 48 months of active enrollment (24 months for phase I and 24 months for the expansion cohorts phase), 24 months of treatment, and 24 months of follow-up.

### Expected treatment-related adverse events

The possible toxicity of a combination of radiotherapy and immunotherapy mainly depends on the location of the irradiation and may involve hepatitis for liver irradiation or autoimmune pneumonitis for lung irradiation. However, such side effects are transitory and manageable. In a phase I study, administration of SBRT before immunotherapy appeared safe with acceptable toxicity. The most common treatment-related adverse events were general disorders and administration site abnormalities. Other frequent mild adverse events (> 20%) included gastrointestinal disorders, metabolism and nutrition disorders, musculoskeletal and connective tissue disorders, and respiratory, thoracic, and mediastinal disorders [19].

### Dose modifications

There will be no dose modifications, including dose reductions for tiragolumab, atezolizumab, or radiotherapy, in this study.

### Management of Adverse Events and treatment interruption

Guidelines for the management of AEs are provided in the supplementary appendix [see Additional file 1]. Atezolizumab and/or tiragolumab may be temporarily suspended as appropriate for the management of toxicity. On the basis of the available characterization of the mechanism of action, tiragolumab may cause adverse events similar to but independent of atezolizumab, may exacerbate the frequency or severity of atezolizumab-related adverse events, or may have non-overlapping toxicities with atezolizumab. Because these scenarios may not be distinguished from one another in the clinical setting, immune-mediated adverse events should generally be attributed to both study drugs, and dose interruptions or treatment discontinuations in response to immune-mediated adverse events should be applied to both tiragolumab and atezolizumab.

Tiragolumab and atezolizumab may be held for a maximum of 12 weeks (or approximately four cycles).

If tiragolumab is interrupted for more than approximately 12 weeks for any reason, the patient will have to permanently discontinue tiragolumab treatment but may continue atezolizumab if there is no contraindication and after discussion with the coordinating investigator to determine whether the toxicity is considered related to tiragolumab and/or to the combination. Continued dosing with single-agent atezolizumab administered to patients will require that all other study eligibility criteria continue to be met. An exception can be made if, in the judgment of the investigator, the patient is likely to derive clinical benefit from resuming tiragolumab after a hold longer than 12 weeks. In this case, tiragolumab may be restarted with the approval of the coordinator of the study by contacting the sponsor for advice.

If atezolizumab is interrupted for more than approximately 12 weeks (or approximately four cycles), the patient will have to permanently discontinue atezolizumab. However, if, in the judgment of the investigator, the patient is likely to derive clinical benefit from atezolizumab after a hold longer than 12 weeks, atezolizumab may be restarted with the approval of the coordinator of the study by contacting the sponsor for advice.

If a patient must be tapered off steroids used to treat adverse events, atezolizumab may be withheld for an additional time beyond approximately 12 weeks from the last dose, and tiragolumab may be withheld for an additional time beyond approximately 12 weeks from the last dose until steroids are discontinued or until steroids are reduced to a prednisone dose (or dose equivalent) ≤ 10 mg/day. The acceptable length of interruption will depend on an agreement between the investigator and the coordinator of the study after contacting the sponsor for advice and approval. Dose interruptions for reason(s) other than toxicity, such as surgical procedures, may be allowed with the coordinator of the study by contacting the sponsor for advice and approval.

After both tiragolumab and atezolizumab have been permanently discontinued, the patient will be monitored for safety and efficacy.

### Study objectives

#### Main objective of the phase I part

The main objective of the phase I study is to evaluate the safety of the SBRT, atezolizumab and tiragolumab Mabs combination in a sequential or concomitant scheme and determine the recommended expansion cohorts phase scheme of administration.

#### Main objective of the expansion cohorts phase

The main objective of the study is to evaluate, among patients treated with the recommended scheme, the efficacy of the SBRT, atezolizumab, and tiragolumab combination in terms of 6-month progression-free survival (PFS).

#### Secondary objective of the expansion cohorts phase

The secondary objectives will be determined by the recommended scheme of administration.

To evaluate the progression-free survival (PFS) following SBRT, atezolizumab, and tiragolumab combinationTo evaluate the long-term safety of SBRT, atezolizumab, and tiragolumab antibodies combinationTo evaluate the overall survival (OS) following SBRT, atezolizumab, and tiragolumab combinationTo evaluate the overall response rate (ORR) and non-progression rate (NPR) following SBRT, atezolizumab and tiragolumab combinationTo evaluate the duration of response (DOR) and non-progression duration (NPD) following SBRT, atezolizumab and tiragolumab combinationTo evaluate the abscopal effect (non-irradiated lesions volume variation).

### Exploratory objectives

To evaluate efficacy as a function of PD-L1, TIGIT, CD155, and CD112 expressionTo evaluate the evolution of the in situ immune responseTo evaluate the evolution of the systemic immune responseTo evaluate the induction of neoantigen and tumor-shared antigen-specific immune responseTo evaluate the radiotherapy planning target volumes (PTV) impact on systemic immune responseTo create a research biosample repository (blood and tumor)

### Study endpoints

#### Primary end-points of phase I

Safety will be evaluated using DLTs (Dose-Limiting Toxicities) that occur:

the first 5 weeks (35 days) after the first dose of study treatment for **sequential** administration (3x8 Gy of radiotherapy and 3 dosings of immunotherapy)the first 4 weeks (28 days) after the first dose of study treatment for **concomitant** administration (3x8 Gy of radiotherapy and 3 dosings of immunotherapy).

DLTs are defined by all events that are deemed related to the study treatments (SBRT and/or tiragolumab and/or atezolizumab), unless there is a clear alternative cause, with CTCAE version 5.0 grade ≥ 3 non-resolutive (return to basal grade) after 14 days. Any grade 5 related to study treatment will be considered a DLT. No clinical trial has combined SBRT, anti-PD-L1, and anti-TIGIT yet. In order to reduce toxicity risk, we will use a non-ablative SBRT dose, and we will begin this trial by first evaluating tolerance using two types of combination schedules. For the first one, immunotherapies will be administered one week after the start of SBRT with at least 2 days between the end of radiotherapy and the injection of immunotherapy. If no DLT is highlighted, we will evaluate the tolerance of our combination administered using the concomitant scheme. The concomitant scheme was designed on the basis of our preliminary data obtained with RT delivered on the same day as immunotherapy initiation. The decision diagram provided in Fig. 3 describes how the scheme of administration will be selected (sequential or concomitant). If safety is validated with the sequential schedule, the concomitant schedule will be assessed. If safety is then validated with the concomitant schedule, this scheme of administration will be selected for expansion cohorts. Otherwise, the sequential schedule will be selected for expansion cohorts. If there is no difference in toxicity, the concomitant schedule will be selected. Safety is defined according to the decision diagram.

**Fig. 3 Fig3:**
[figure not shown]
Decision diagram. Algorithm for assessment of sequential schedule (left panel) and concomitant schedule (right panel)

For the **sequential schedule**, safety is defined by:

0 or 1 patient over 6 displays a DLT**or** 2 patients over 6 display a DLT, then 0 over 3 new included patients display a DLT

For the **concomitant schedule**, safety is defined by:

0 or 1 patient over 6 displays a DLT**or** 2 patients over 6 display a DLT, then 0 over 3 new included patients display a DLT

#### Primary endpoint of the expansion cohorts phase

Efficacy will be evaluated using the 6-month PFS. PFS is defined as the time from inclusion to the first occurrence of disease progression, as determined by the investigator according to RECIST v1.1 and iRECIST, or death from any cause, whichever occurs first. It will be evaluated at 6 months.

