#### Secondary endpoints

Every secondary endpoint will be determined for patients included in the recommended scheme administration (expansion phase):

PFS according to RECIST v1.1 and iRECIST, or death from any cause, whichever occurs first. It will be evaluated at 12 months. Additionally, the median will also be displayed.Long-term safety of the SBRT, atezolizumab, and tiragolumab antibody combination will be evaluated with acute and late adverse events (AAEs) according to CTCAE 5.0.Acute adverse events are adverse events occurring within the first sixth months, and late adverse events are adverse events occurring after the first six months.Overall survival (OS) is defined as the time from inclusion to death from any cause.Overall response rate (ORR) and non-progression rate (NPR) are evaluated from the first two evaluation scanner images carried out at 9 and 18 weeks after time from inclusion (CT-scan forecast before the 3rd and 6th cure) as determined by the investigator according to RECIST v1.1 and iRECIST. Overall response is defined by a partial or complete response. Non-progression is defined by a partial or complete response and a stable disease.Duration of response (DOR) is defined as the time from documentation of a disease complete or partial response to disease progression, defined according to RECIST v1.1 and iRECIST. Non-progression duration (NPD) is defined as the time from documentation of a complete response, partial response, or stable disease to a disease progression, as defined according to RECIST v1.1 and iRECIST.Abscopal effect is evaluated following non-irradiated metastasis volume(s) from scanner images.

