#### Definition of study population analysis

The safety population is defined by all patients who received at least 1 dose of immunotherapy combined with at least 1 radiation therapy session.

The modified-intention-to-treat (mITT) population is defined by all patients treated with the phase I recommended scheme who received at least one administration of each immunotherapy, the 3 radiotherapy fractions, and at least one tumor evaluation (CT-scan).

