#### Statistical analysis of endpoints

The primary endpoint will be evaluated in the safety population. Secondary efficacy endpoints will be evaluated in the mITT population, and secondary safety endpoints in the safety population.

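### PFS and OS are counted from inclusion but analysed only in patients who were later treated, so 6-month PFS is biased upward by any lag before treatment

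*Protocol article*

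**What the plan says.** - **Time origin.** Under Primary endpoint of the expansion cohorts phase: "PFS is defined as the time from inclusion to the first occurrence of disease progression". Secondary endpoints gives OS the same origin.
- **Population, primary endpoint.** Under Statistical analysis of endpoints: "The primary endpoint will be evaluated in the safety population". Definition of study population analysis describes that set as "all patients who received at least 1 dose of immunotherapy combined with at least 1 radiation therapy session".
- **Population, secondary efficacy.** The mITT set, made up of patients on the recommended scheme "who received at least one administration of each immunotherapy, the 3 radiotherapy fractions, and at least one tumor evaluation (CT-scan").
- **Estimator.** The Expansion cohort paragraph specifies Kaplan-Meier for PFS and OS.
- **Timing.** Response scans are "carried out at 9 and 18 weeks after time from inclusion (CT-scan forecast before the 3rd and 6th cure"). Phase I design sets infusions every 21 days. Progression of the study adds: "The study will start with a 28-day baseline phase". The article does not say where inclusion falls in that phase, or how long after inclusion treatment begins.

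**The concern.** Inclusion is a sound origin if every included patient is analysed. First treatment is a sound origin if only treated patients are analysed. The article takes the origin from one and the population from the other. Patients lost to death or deterioration before treatment disappear from the analysis, and those who reach treatment are credited with the weeks it took to get there. Both effects raise the estimate.

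These are single-arm cohorts meant to show a signal of activity, with planning rates set against published rates. An error that always favours the combination is not covered by the confidence interval, which describes random error only.

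OS in the mITT set is affected more, because a patient must survive to a CT evaluation to be counted at all.

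**Working it through.** **1. The plan's own figure, as a yardstick.** The article gives no figure for the lag or its effect. It does give a precision: 20 × 0.9 = 18 evaluable patients, and 95% CI half-widths of 22, 23 and 24 points at 6-month PFS of 35% (head and neck), 30% (renal) and 45% (lung). Exact (Clopper-Pearson) half-widths at 6/18, 5/18 and 8/18 are 22.8, 21.9 and 23.9 points. The stated set is recovered with the first two values interchanged, which is a separate matter. Random error is thus about 22 to 24 points either way.

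**2. How long is the lag?** With 21-day cycles, infusion 3 falls 6 weeks after infusion 1, and infusion 6 falls 15 weeks after it.
- Scans literally before infusions 3 and 6: 9 − 6 = 3 and 18 − 15 = 3, so about 3 weeks from inclusion to first infusion.
- Scans meant after three and six completed cycles: 9 − 3 × 3 = 0 and 18 − 6 × 3 = 0, so no lag.

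The text does not settle which is meant.

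**3. Compared with all included patients.** Let p be the 6-month PFS in everyone included, and f the share lost before treatment through death or deterioration, counted as failures. The treated-only rate is p/(1 − f). The values of f are assumptions.

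| f | p = 35% | p = 30% | p = 45% | Overstatement (points) |
|---|---|---|---|---|
| 2% | 35.7% | 30.6% | 45.9% | 0.6 to 0.9 |
| 5% (1 in 20) | 36.8% | 31.6% | 47.4% | 1.6 to 2.4 |
| 10% | 38.9% | 33.3% | 50.0% | 3.3 to 5.0 |

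The last row is a ceiling: it treats the article's entire 10% non-evaluable allowance as failures before treatment.

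**4. Compared with PFS counted from first treatment.** Let p be the 6-month rate from first treatment, with a constant hazard and a lag of g months. Counted from inclusion, 6 months covers only 6 − g months on treatment, so the rate reads p^((6 − g)/6). For 3 weeks, g = 21/30.44 = 0.69, the exponent is 0.885, and 0.35^0.885 = 0.395.

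| Lag | p = 35% | p = 30% | p = 45% | Overstatement (points) |
|---|---|---|---|---|
| 0 | 35% | 30% | 45% | 0 |
| 1 week | 36.4% | 31.4% | 46.4% | 1.4 |
| 2 weeks | 37.9% | 32.9% | 47.8% | 2.8 to 2.9 |
| 3 weeks | 39.5% | 34.5% | 49.3% | 4.3 to 4.5 |

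Replacing the constant hazard by Weibull shapes 0.8 to 1.3 at 3 weeks gives about 3.5 to 6 points. The formula is smooth, whereas progressions are found at scans, so the realised shift would depend on where scans fall relative to 6 months.

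**5. mITT.** Entry needs all three fractions and a CT evaluation, the first planned at week 9. A patient who dies before any scan is excluded, yet OS time for the others starts at inclusion. The article gives nothing from which to size this.

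**The case against.** **The lag may not exist.** The 3 weeks rest on one phrase, and weeks 9 and 18 equal three and six completed cycles exactly. The article's cycle counts are also loose elsewhere: the DLT section places three immunotherapy dosings within 28 or 35 days on a 21-day cycle. This stands, so 3 weeks is one reading and not a finding.

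**The baseline phase suggests 4 weeks.** A reader might infer a lag of up to 28 days. The article does not support that. Eligibility relies on screening tests and on lesions being plannable within the organ constraints, so the phase plausibly ends at inclusion.

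**The interval is free of all events.** A reader might infer this too, and it goes too far. A patient whose progression is documented before treatment but who is still treated stays in the set and counts. Growth during the lag would be found at the week 9 scan. What is removed is death, or deterioration that prevents treatment, and entry requires performance status 0 or 1 and life expectancy above 6 months.

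**The bias differs by scheme.** This does not follow either. On the literal reading the first infusion comes about 3 weeks after inclusion in both schemes, the safety population needs both treatments, and only one scheme goes forward.

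**The size is small.** Under a constant hazard, a 3-week lag would mean losing 9% to 13% of included patients to events before treatment, against a 10% allowance for all causes. Measured against all included patients, 1 to 2 points is therefore more plausible. No efficacy threshold depends on the estimate. This limits the weight of the point but does not remove the mismatch.

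**It can be left to the analysis plan.** The article itself fixes both origin and population, and they do not fit. If the primary-endpoint sentence were meant for phase I only, the other defined set, mITT, is also treated-only and stricter.

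**Conclusion.** The point holds as a mismatch of origin and population with an upward bias of uncertain, modest size.

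- Compared with all included patients: about 0.6 to 0.9 points if 2% are lost before treatment, and 1.6 to 2.4 points if 5% are.
- Compared with PFS from first treatment under a constant hazard: about 1.4 points at 1 week and 4 to 5 points at 3 weeks.
- With no lag: zero.

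The loss shares and the lag are assumptions, because the article states neither. The shift is well inside the interval half-width and changes no stated decision, but it runs in one direction and is avoidable. OS in the mITT set is more exposed, by an amount that cannot be computed from the article.

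**What to change.** 1. Choose one pairing and use it for PFS and OS: either count from first study treatment in the treated-only populations, or keep inclusion as origin and analyse all included patients, with deaths before treatment counted as events.
2. State which date is inclusion and which is first study treatment. The safety population requires both radiotherapy and immunotherapy, so if the sequential scheme is selected and the clock starts at the first fraction, about one week before the first infusion remains. The definition should say how that week is handled.
3. A new origin does not remove the effect of the CT requirement on OS. Analyse OS in the safety population or in all included patients.
4. Reconcile the scan weeks with the cycle numbers in Secondary endpoints, and anchor the scans to the chosen origin.

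The cost is a few sentences of definition. No new data are needed for the first option, since the DLT windows already run from the first dose. The reported rate may become slightly less favourable.
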